**Main Ethical Issues**

*Confidentiality*

The participants will be employees of the NHS primary care organisations in which this research is occurring. They will rate questionnaires capturing information about their well-being, and mood in relation to their working lives. Consequently, it is of paramount importance that the information they give within the questionnaires is confidential. Thus, upon entry to the study - after giving consent - participants will be generate a reference number for themselves (first two letters of mother's maiden name and last four digits of mobile number). This will allow us to separate data given within questionnaires from participant’s contact details and demographics. Once they have given consent their contact details and demographics will be kept on one database, alongside their reference number. A separate database will contain the questionnaire data linked to the reference number alone. This reference number will be used on all data captured in online surveys. They will not enter any personally identifiable information alongside questionnaire data (name, address etc.). In addition, online survey data will be collected via an encrypted website (Bristol Online Surveys). There will also be the opportunity to complete hard-copies of the questionnaires before or after the intervention. Here questionnaires will be completed at the location of the training sessions. Hard-copies of the questionnaire will hold no person identifiable information; they will require only the anonymised participant information number alongside questionnaire responses. Mindfulness practitioners will return hard-copies of the questionnaires to the research team at the University of Leeds, these questionnaires will be stored in secure filing cabinets in locked offices within the university.

Only the research team ([name], [name] and [name]) will have access to person identifiable data. This will be safely stored on a University-issued password protected computer. In addition, to maintain confidentiality amongst participants, the requirement of confidentiality during the training sessions will be emphasized at the beginning of each session. Participants will also be informed that they do not have to share personal information during the training sessions. There will be flexibility in allocating participants to alternative training sessions if they request not to attend with a close colleague or manager. A random selection of training sessions will be recorded to evaluate trainer adherence to the intervention protocols. In this case, participants will be asked for their consent at the beginning of the session. Recordings of training sessions will not be transported, will be uploaded immediately to a university password protected computer via the "desktop anywhere" programme - as accessed by a university laptop. After uploading the session will be erased from the recording device. Recordings of training sessions will also be stored securely on a University computer.

Note, in line with open science initiatives we will, after an embargo period of three years, store the anonymised data within the University of Leeds research data repository.

*Managing Risk*

Based on previous experience of similar intervention research in the workplace (e.g., Flaxman & Bond, 2010), the risk of harm to participants is minimal. No problems have been reported during several similar intervention studies conducted by [name] over the past 10 years (including recent studies conducted in other NHS trusts). As stated, past experience, and the focus of the training on occupational functioning as opposed to childhood traumas and wider mental health problems suggests that the disclosure of significant risks (e.g. immediate plans for suicide) or safeguarding issues (e.g risk of harm to vulnerable others) is unlikely. Nonetheless, we cannot rule-out the occurrence of such an event; therefore, we have an agreed escalation protocol (included). This escalation protocol has been approved by local Medical and Nursing Directors in line with ethical guidance for health practitioners relating to risks to their own health and that of other people. Participants and trainers will be asked to

agree to the escalation protocol prior to the intervention.

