**METHODS**

*Design*

The study will employ a randomised controlled design to examine the effectiveness of a group-based ACT training programme for improving the well-being of NHS staff, compared to a wait-list control group.

*Participants*

Participants will be primary care staff within the NHS in Leeds and West Yorkshire. There will be one inclusion criterion: currently employed by the NHS and working within NHS primary care settings in Yorkshire and Humber. There will also be one exclusion criterion: not presently at work.

Based on sample sizes from other ACT studies in similar settings (e.g., Flaxman & Bond, 2010; Flaxman et al., 2016) we aim to recruit 140 people.

*Procedure*

Recruitment: The study will be advertised to potential participants via local awareness raising in primary care settings. Participants will be given information about the study and will be given the e-mail address of a member of the research team (NHS e-mail) to contact a member of the research team if interested in opting-in to the study.

Once participants have expressed an interest in the study, they will immediately be sent the participant information sheet (PIS) via e-mail, which outlines the nature of the research and training. After having had at least 24 hours to consider the information presented in the PIS, consent will be taken online. A consent form will be the first sheet of the pre-intervention questionnaire. Immediately after giving consent participants will then enter demographic details and generate their own individual participant number (First two letters of their mother's maiden name initials and the last four digits of their telephone number). This reference number will be used to complete all online questionnaire batteries.

Participants will be informed that they will shortly be randomly allocated to begin the training, the first session beginning in late September 2017, or to the waitlist control group. As soon as an initial 40 people have volunteered, the first randomisation process will take place, allocating volunteers to the ACT training programme or to the waiting list control group. Participants allocated to the training group will then receive dates, times, and locations of the scheduled training sessions. Participants will be randomised to groups by the research team using a computer generated randomisation procedure.

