Those allocated to the waiting list control will begin the training in Feb /March 2018. These participants will receive an email (or letter) providing reasons for being allocated to the later training group (i.e., limitations on the number of people that can be trained at one time, and the need to rigorously evaluate the impact of the training on staff well - being). All participants will be required to complete an online questionnaire battery (described in more detail below) on four separate occasions over the 14 week evaluation period. They will be e-mailed the questionnaire at the appropriate time-point, if they don’t complete the questionnaire within three days, they will be sent a reminder e-mail.

*Intervention*

The intervention will be based on an existing standardised ACT protocol designed for workplace settings. Participants will be invited to attend a total of four two-hour group sessions; these sessions will occur on four consecutive weeks.

Each session will consist of between 8 and 15 people. Training sessions will be delivered by experienced clinicians, who are also trained mindfulness teachers either on the national register or who comply with the Good Practice Guidelines. These trainers will be taught to deliver the study’s ACT intervention over a minimum of two training days with [name], who has extensive experience training professionals to deliver workplace interventions based around ACT. They will be supervised by [name] and by a professional mindfulness supervisor.

*Measurement*

A questionnaire battery will be administered to participants on four occasions:

1. Pre-intervention: minus 1 to 2 weeks

2. Mid-intervention: between sessions 2 and 3 of the intervention (week 3)

3. Post-intervention: one week after session 4 (week 5)

4. Follow-up: 3 months after post-intervention (week 19)

The questionnaire battery will take approximately 25 minutes to complete on each occasion. These on line questionnaires will be completed via encrypted survey software (known as Bristol Online Surveys) hosted by the CI’s institution (University of Leeds). Each participant will receive an email containing a link to the questionnaires. Those allocated to begin the training in in September 2017 will be e-mailed the questionnaires to complete prior to training.

*Primary outcome*

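### Paper questionnaires completed at the training venue and returned by trainers are, around week 5, open in practice only to the ACT arm

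*Protocol*

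**What the plan says.** The Protocol (METHODS, Measurement) sets a common default. Every participant is e-mailed a link to an online survey on four occasions: before training, in week 3, in week 5 and in week 19. The third is fixed as "Post-intervention: one week after session 4 (week 5".

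Main Ethical Issues, Confidentiality, then adds a second route:

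- On whether paper is available: "There will also be the opportunity to complete hard-copies of the questionnaires before or after the intervention"
- On where such forms are filled in: "Here questionnaires will be completed at the location of the training sessions"
- On how they reach the study team: "Mindfulness practitioners will return hard-copies of the questionnaires to the research team at the University of Leeds"

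Under METHODS, Intervention, the session leaders are described in similar terms: "Training sessions will be delivered by experienced clinicians, who are also trained mindfulness teachers".

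METHODS, Procedure, gives the dates. For the ACT group it has "the first session beginning in late September 2017". For the comparison group it says "Those allocated to the waiting list control will begin the training in Feb /March 2018".

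**The concern.** A paper form that has to be filled in at the training venue is useful only to someone with a reason to be there. While the arms are being compared after training, that means ACT participants. Paper is not formally restricted to one arm, but place and dates together have nearly that effect, and nothing in the document makes the route equal.

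The primary outcome, the GHQ-12, is a self-report of distress by people who know whether they have been trained or are still waiting. If some ACT participants answer on paper at the venue and pass the form to the practitioners, while controls answer online, the arms can differ in setting, in who handles the answers and in when the answers are given. Easier completion in one arm could also make response unequal. METHODS, Analyses, imputes missing data by last value carried forward, so unequal response would enter the comparison directly.

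**Working it through.** **Step 1: calendar.** Inputs are four sessions in consecutive weeks, assessments in weeks 5 and 19, an ACT start in late September 2017 and a wait-list start in February or March 2018. Counting session 1 as week 1, session 4 is 3 weeks later, week 5 is 4 weeks later and week 19 is 18 weeks later. The exact start is not given, so I take 18 to 29 September as the assumed range.

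| Event | Start 18 Sept | Start 29 Sept |
|---|---|---|
| Session 4 | 9 Oct 2017 | 20 Oct 2017 |
| Week 5 | 16 Oct 2017 | 27 Oct 2017 |
| Week 19 | 22 Jan 2018 | 2 Feb 2018 |
| Earliest wait-list session | 1 Feb 2018 | 1 Feb 2018 |

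From the latest week-5 date (27 October) to 1 February is 4 + 30 + 31 + 31 + 1 = 97 days. At week 5 no wait-list participant has had a session, and none is due for nearly 14 weeks. Week 19 falls before, or right at, the earliest wait-list start, so the separation is less firm there.

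**Step 2: timing.** The last session is in week 4 and the assessment is in week 5. A form completed at session 4 is therefore 5 − 4 = 1 week early. The work-related worry scale asks about the past week, so such a form would also cover a different week from a control's week-5 form.

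**Step 3: which assessments are exposed.**

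- Pre-intervention: consent is taken online as the first sheet of this questionnaire, before randomisation, so it appears to be online in both arms.
- Week 3: it falls between the second and third sessions and is not clearly covered by a paper option placed before or after the intervention.
- Week 5: exposed, for the ACT arm only.
- Week 19: ACT sessions ended about 15 weeks earlier (19 − 4), and wait-list sessions may be about to start.

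**Step 4: size.** The Protocol gives no paper uptake, mode effect, effect size, SD or allocation ratio, so there is no figure to reproduce. What follows is illustration on assumed values only.

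Bias in SD units = share of the ACT arm on paper × shift in score. For the planned 140, assume 70 per arm. Then SE = √(2/70) = 0.169, and the two-sided type I error = 1 − Φ(1.96 − bias/SE) + Φ(−1.96 − bias/SE).

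| Share on paper | Shift (SD) | Bias (SD) | Type I error (nominal 5%) |
|---|---|---|---|
| 25% | 0.1 | 0.025 | 5.3% |
| 50% | 0.1 | 0.05 | 6.0% |
| 50% | 0.2 | 0.10 | 9.1% |
| 50% | 0.3 | 0.15 | 14.4% |
| 100% | 0.3 | 0.30 | 42.7% |

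For response, suppose both arms change by c and every missing value is replaced by baseline. The bias is then c × (ACT response − control response). With c = 0.2 and response of 90% against 80%, it is 0.2 × 0.10 = 0.02 SD. With c = 0.4 and 90% against 70%, it is 0.4 × 0.20 = 0.08 SD.

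**The case against.** Paper is an optional extra, mentioned in a passage on confidentiality. Both arms share the same online default and the same reminder after three days. Uptake may be very low, and then the bias is negligible. Paper forms carry only a self-generated reference number and no identifying details, which weakens the worry about trainers handling answers. All of this stands and limits the weight of the point. None of it equalises the route between arms.

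Several stronger readings are tempting, but the document does not support them:

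- *That the paper route contradicts the assessment schedule.* The text names a place and a loose time, not session 1 or session 4. Someone could go to the venue in the scheduled week, although no such visit is described.
- *That forms are completed in front of the trainers.* The text says only that mindfulness practitioners return them. That these are the trainers is the natural reading, but still an inference.
- *That every assessment is affected, in the ACT arm alone.* Exposure is clear only around week 5. Wait-list participants could reach paper at their own first session, close to week 19, and dates for groups after the first randomisation are not given.
- *That response will be higher in one arm.* This is possible, not stated.
- *That no analysis could address it.* Paper forms can be identified, so a sensitivity analysis is feasible, though people choose paper for themselves and that would limit it.
- *That the bias is a definite fraction of the expected effect.* Uptake, shift and effect would all have to be assumed.

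**Conclusion.** The point holds in a limited form. Around the week-5 assessment, the Protocol offers a way of answering that is tied to the training venue and passes through practitioners, at a time when only the ACT arm has sessions behind it and the wait-list arm has none for months. If it is used at session 4, the answers are also about a week early. This permits an avoidable difference between arms in mode, timing, handling and possibly response for an unblinded self-reported primary outcome.

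The conclusion rests on the stated dates, on the first training group, and on reading the mindfulness practitioners as the trainers. The size is unknown. The illustration runs from a trivial bias (0.025 SD) to a serious one (0.30 SD), and nothing in the Protocol says where in that range the trial would fall. Where, when and through whom outcomes are collected is for the protocol to settle; a statistical analysis plan could describe the consequences but not remove them. It is a worthwhile improvement because it is cheap, not because a large bias has been shown.

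**What to change.** In Main Ethical Issues, Confidentiality, delete completion at the training venue and return through mindfulness practitioners. Keep the online survey as the default. Where someone needs paper, offer it to participants in either arm, sent on the same dates as the online link and returned directly to the university team. Record mode and completion date for every questionnaire, so that departures from the schedule can be seen and a sensitivity analysis is possible.

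The cost is a change of wording, minor postage and possibly slightly lower response in the ACT arm. A lighter alternative is to keep some paper collection, provided that it is offered equally to both arms and handled by staff who do not deliver the training.
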